### Data management

This project employs a web-based data management system for data entry. Prior to data collection, data entry personnel will receive specialized training based on a predefined Data Entry Guideline. All entered data will undergo rigorous verification according to the Data Validation Plan, utilizing both automated system checks and manual medical reviews. Any database modifications are fully documented with timestamps, personnel identification, and rationale. Before database lock, the data management unit prepares a comprehensive Data Management Report for sponsor review and approval. During the Data Review Meeting, stakeholders (data managers, statisticians, investigators) discuss critical elements—including subject disposition, protocol deviations, potential outliers, baseline characteristics, efficacy endpoints, and finalization of the Statistical Analysis Plan (SAP)-based on the Data Management Report and data listings, culminating in data review resolutions. The locked database is delivered to statisticians in SAS transport files (.xpt format) accompanied by dataset specifications and codebooks for statistical analysis.

#### Quality control

The development of the protocol has been informed by iterative refinement and critical evaluation from a multidisciplinary team of acupuncture, methodological, and statistical experts. We developed comprehensive Standard Operating Procedures (SOPs) covering intervention delivery, Case Report Form (CRF) completion, outcome assessment, and data management. All personnel received standardized training to ensure protocol compliance. A comprehensive quality control system will be implemented, including random patient verification via telephone audits and spot checks of researchers’ informed consent documentation. Acupuncture protocol fidelity will be prioritized, with monitoring of: Practitioner certification for this trial, Acupoint localization accuracy, Sterilization compliance, Needling depth/technique standardization, Manipulation consistency.Verification methods will include direct observation, simulated procedure assessments, and practitioner interviews.

#### Sample size

Based on previous research (21, 22), we estimated that the CPR of IVF-ET in DOR patients after acupuncture pretreatment would be 38%, compared to 22% following placebo acupuncture pretreatment. A sample size of 120 participants per group has been determined to ensure 80% statistical power, with a two-sided alpha of 0.05. An initial total of 300 participants (150 per group) will be enrolled to allow for an anticipated 20% dropout rate.

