### Outcome measurement

#### Primary outcome

The primary outcome is the CPR following the first fresh or frozen embryo transfer. Ultrasonographic identification of a gestational sac and fetal heartbeat at 28 days post-embryo transfer confirmed a clinical pregnancy. The CPR is defined as the proportion of clinical pregnancies to the total number of embryo transfer cycles.

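### At 38% versus 22%, 120 women per group give about 77.5% to 78.4% power, not the stated 80%, which needs about 125 to 128 per group

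*Protocol article*

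**What the plan says.** The Sample size section of the protocol article assumes that "the CPR of IVF-ET in DOR patients after acupuncture pretreatment would be 38%, compared to 22% following placebo acupuncture pretreatment". It then concludes: "A sample size of 120 participants per group has been determined to ensure 80% statistical power, with a two-sided alpha of 0.05". The enrolment target follows: "An initial total of 300 participants (150 per group) will be enrolled to allow for an anticipated 20% dropout rate". It names no formula or software and does not define dropout. The Randomization method section gives 1:1 allocation.

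Three other places bear on what the 120 represents. The Primary outcome section states: "The CPR is defined as the proportion of clinical pregnancies to the total number of embryo transfer cycles". The Statistical analysis section applies the intention-to-treat principle to all analyses, with multiple imputation for missing data. Table 4 lists cycle cancellation as a secondary outcome, and no expected rate is given for it.

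**The concern.** The Sample size section gives both rates, the alpha and its sidedness, the power and the number per group. With the 1:1 allocation, the calculation can be repeated from the article alone, and the figures do not agree. A reader of a null result would credit the trial with a power that its own assumptions do not deliver at 120 per group. The error also passes into the enrolment total, because 150 per group is built on 120.

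A second matter is one of clarity. The section counts participants, whereas the outcome counts transfer cycles. The text does not tie the two assumed rates to either denominator.

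**Working it through.** **Inputs** (Sample size section, except allocation): p1 = 0.38, p2 = 0.22, difference d = 0.16, mean rate 0.30; two-sided alpha 0.05 (z = 1.960); power 80% (z = 0.8416); 1:1 allocation; 120 evaluable per group; 20% dropout.

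**Step 1: try to reproduce 120.**

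- Standard deviation terms: √(2 × 0.30 × 0.70) = 0.6481, and √(0.38 × 0.62 + 0.22 × 0.78) = √0.4072 = 0.6381.
- Pooled: n = (1.960 × 0.6481 + 0.8416 × 0.6381)² / 0.16² = (1.2702 + 0.5371)² / 0.0256 = 127.6, so 128.
- Unpooled: n = 0.4072 × (1.960 + 0.8416)² / 0.0256 = 124.8, so 125.
- Arcsine: n = 2 × (1.960 + 0.8416)² / 0.3520² = 126.7, so 127.
- Log-odds (Wald): 131.2, so 132.
- Pooled with continuity correction: 140.
- One-sided, for completeness: 101, or 113 with continuity correction. This would also contradict the stated two-sided alpha.

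None of these gives 120.

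**Step 2: power at 120 per group.**

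- Pooled: (0.16 × √120 − 1.2702) / 0.6381 = (1.7527 − 1.2702) / 0.6381 = 0.756, so power is 77.5%.
- Unpooled: 1.7527 / 0.6381 − 1.960 = 0.787, so power is 78.4%.
- Arcsine: 77.8%.
- Exact binomial enumeration: chi-square 77.7%, likelihood ratio 78.2%, Wald test of the difference 78.3%.

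Each falls short of 80%, by 1.6 points (unpooled) to 2.5 points (pooled).

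**Step 3: dropout.** 120 / 0.8 = 150, so the inflation is done correctly. With the recomputed numbers it would be 125 / 0.8 = 156.25, so 157 per group (314 in total), or 128 / 0.8 = 160 per group (320 in total). The plan has 300.

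**Step 4: power if all 150 per group are evaluable.** Pooled: (0.16 × √150 − 1.2702) / 0.6381 = 1.080, so 86.0%. Unpooled: 86.7%.

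**Step 5: what the denominator could do.** The protocol gives no share of women without a transfer, so the 10% to 20% below is an assumption, used only to show how far the reading matters. Pooled power:

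| Reading | Power |
|---|---|
| Women without a transfer are already within the 20% (120 per group left) | 77.5% |
| They come on top of a full 20% dropout, 10% to 20% (108 to 96 per group) | 73.1% to 67.9% |
| They are the only loss from 150, 10% to 20% (135 to 120 per group) | 82.2% to 77.5% |
| All 150 analysed, no transfer counted as not pregnant, 10% to 20% | 80.5% to 74.0% |

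The protocol does not say which row applies.

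**The case against.** **Rounding.** The rates are printed as whole percentages and come from two cited sources. Unrounded values could lead to about 120: 38.25% against 21.75% gives 119.9 (pooled), and 38.3% against 22.0% gives 120.5 (unpooled). This stands as a possible explanation and shows how small the gap is. It does not rescue the paragraph, because the stated rates are 38% and 22%, and rounding could equally have raised the number: 37.5% against 22% needs 136.

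**Consequence.** A null result would be read much the same at 78% power as at 80%. Under intention to treat with imputation, the analysed number may also be nearer 150 than 120, where power exceeds 80% at the stated rates. Both remarks are fair. They limit the importance of the error but do not make the stated figure correct.

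**The stronger reading.** A reader might infer that power is lower still, perhaps 68% to 73%, because cancelled cycles take the evaluable number below 120. The document does not support that. Dropout is undefined, and nothing places women without a transfer outside the 20%. Listing cycle cancellation as an outcome does not show that the allowance omits it. The range comes from stacking an assumed share on top of the full 20%, and other readings in the table leave power unchanged or above 80%.

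**Conclusion.** The statement is wrong as written. At exactly 38% and 22%, two-sided alpha 0.05 and 1:1 allocation, 120 evaluable women per group give about 77.5% (pooled) to 78.4% (unpooled) power. Reaching 80% takes about 125 to 128 per group. This is a small arithmetic error to correct and does not amount to a serious loss of power. The conclusion uses only figures printed in the article and does not depend on how women without a transfer are handled.

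On the denominator, the supportable point is that the Sample size section leaves open whether the rates are per transfer or per randomised woman, and what the 20% covers. No size can be attached to that from the document.

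**What to change.** Reword the Sample size section in one of two ways:

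- State that 120 evaluable women per group give about 77.5% power (pooled variance; 78.4% unpooled) for 38% versus 22%, and that 150 per group give about 86%; or
- Give the unrounded rates and the formula that yield 120.

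In the same paragraph, state whether 38% and 22% are per embryo transfer or per randomised woman, and whether the 20% allowance includes women who have no transfer.

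The cost is a few sentences, and under the first option a slightly less favourable stated power. Enrolment and conduct stay as they are.

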#### Statistical analysis

Analyses will be performed using SAS version 9.3 (SAS Institute Inc., Cary, NC, USA). The intention-to-treat (ITT) principle will be applied to all data analyses in this study. Multiple imputation will be employed to manage missing data. Continuous variables will be reported as mean ± standard deviation or median (interquartile range), and categorical variables as frequencies (percentages).

The primary outcome, CPR, was analyzed using multivariate logistic regression to calculate adjusted odds ratios (aORs) with 95% confidence intervals (CIs). The dependent variable in the model was clinical pregnancy (yes/no), and the independent variable was group allocation. The selection of covariates for adjustment was based on their established clinical relevance to IVF outcomes and any observed baseline imbalances between groups (p < 0.10). These covariates may include centers, age, baseline FSH level, AFC, COH protocol, number of retrieved oocytes, type of ET, number of embryos transferred, etc. Model fit was assessed using the Hosmer-Lemeshow test, and multicollinearity was evaluated via variance inflation factors. Additionally, a Per-Protocol (PP) analysis for priamry outcome will be performed as a sensitivity analysis. Other between-group comparisons will be performed using independent t-tests/Wilcoxon rank-sum tests for continuous data and chi-square/Fisher’s exact tests for categorical data, as appropriate. A two-sided *p* < 0.05 will define statistical significance.

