#### Randomization method

Randomization will be performed after obtaining informed consents. A secure online computerized randomization system will be utilized for randomization to ensure allocation concealment. This centralized web-based platform incorporates multiple functional modules for randomization, data entry, and management, and will be overseen by an independent statistical team. Qualified participants will be assigned to the acupuncyure or placebo acupuncyure groups in a 1:1 allocation ratio, employing stratified block randomization by age (< 35 years vs. ≥ 35 years) through a computer-generated system. Upon enrollment of eligible subjects, personnel responsible for randomization will log into the central randomization system via the internet to obtain a randomization number.

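### Primary-model covariates are chosen partly by chance baseline imbalance from an open list, and age, the stratification factor, is not guaranteed a place

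*Protocol article*

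**What the plan says.** All places are in the protocol article.

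- **Statistical analysis.** The primary outcome is analysed by logistic regression, reported as an adjusted odds ratio. The only term fixed for the model is the treatment term: "the independent variable was group allocation". Adjustment covariates are selected on two grounds, clinical relevance to IVF outcomes and "any observed baseline imbalances between groups (p < 0.10". The candidates are given as an open list: "These covariates may include centers, age, baseline FSH level, AFC, COH protocol, number of retrieved oocytes, type of ET, number of embryos transferred, etc".
- **Randomization method.** Allocation is 1:1, "employing stratified block randomization by age (< 35 years vs. ≥ 35 years) through a computer-generated system". No other stratification factor is named.
- **Data management.** A Data Review Meeting of data managers, statisticians and investigators covers, among other items, baseline characteristics, "efficacy endpoints, and finalization of the Statistical Analysis Plan (SAP)-based on the Data Management Report and data listings". The section does not say whether the meeting is blinded to arm.
- **Blinding.** Participants, efficacy evaluators and statistical analysts are blinded. Acupuncturists are not.

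**The concern.** In a properly randomised trial any baseline difference between arms is a chance event. A test at p < 0.10 therefore detects chance and says nothing about whether the covariate predicts pregnancy. It can bring in a weak covariate that happens to differ and gives no reason to include a strong one that happens to be balanced. Clinical relevance is also a ground for inclusion, but the text names no covariate that must enter on that ground.

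Three consequences follow.

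1. The primary model is not fixed before the data are split by arm, because a between-arm baseline test needs at least coded arm labels.
2. Age defines the randomisation strata, yet it is only a possible covariate, and the stratum itself (<35 or ≥35) is not mentioned in the analysis. Adjustment for the design factor is not guaranteed.
3. The odds ratio is non-collapsible: with prognostic covariates, the conditional odds ratio differs from the unadjusted one even under perfect balance. A different covariate set estimates a different quantity.

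The open list also includes three items that arise after randomisation: retrieved oocytes, type of transfer and number of embryos transferred. Treatment may affect them, and the number of retrieved oocytes is itself a secondary outcome.

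**Working it through.** The plan gives no figure of its own on this point, so there is none to reproduce. Two checks were made.

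**1. How often would chance change the model?**

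Inputs, from the Statistical analysis section: a threshold of 0.10, and five listed items that can be treated as baseline (centre, age, baseline FSH, AFC and COH protocol, the last because it is an entry criterion). Retrieved oocytes, type of transfer and number of embryos transferred are left out, because they cannot show a baseline imbalance.

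With k independent baseline tests and no true differences, P(at least one flag) = 1 − 0.9^k.

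- k = 4 (for example, without centre): 1 − 0.9^4 = 1 − 0.6561 = 0.344, or 34%.
- k = 5: 1 − 0.9^5 = 1 − 0.5905 = 0.410, or 41%.

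Under independence, 41% is an upper figure for the five named items, because stratification by age makes an age flag less likely than 10%. Items added under the open end of the list are not counted.

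**2. What does this do to type I error?**

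Null simulation with no treatment effect and 3,000 trials per scenario:

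- 300 women, the planned enrolment.
- Ages spread evenly over 20–39, with 1:1 permuted blocks within the two age strata (block size of four assumed).
- Four baseline covariates: standardised age and three independent standard normal variables.
- Assumed log-odds effects per standardised unit of −0.5, −0.3, 0.4, 0.3 (moderate) or −0.9, −0.5, 0.7, 0.5 (strong). The documents do not give these.
- Centre and post-randomisation items were not simulated.

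The Monte Carlo standard error near 5% is √(0.05 × 0.95 / 3000) = 0.004, or 0.4 percentage points.

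| Primary model | Moderate effects | Strong effects |
|---|---|---|
| Arm only | 4.6% | 4.8% |
| Arm + age, pre-specified | 4.9% | 5.5% |
| Arm + all four, pre-specified | 4.4% | 5.5% |
| Covariates with baseline p < 0.10, applied mechanically | 4.2% | 4.1% |
| Most favourable of the 2^4 = 16 subsets | 8.1% | 10.6% |

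The pre-specified models are nominal within simulation error. The mechanical rule is slightly conservative. Only free selection after seeing results inflates the error.

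**Reading the sections together.** If the meeting that finalises the SAP has no arm labels, the imbalance test cannot be run there and the covariate set is still open when the SAP is final. If it has labels, even coded ones, the primary model is settled with data split by arm beside a discussion of efficacy endpoints. In neither case is the covariate set fixed in advance.

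**The case against.** The strongest reply is that the plan is less loose than the imbalance phrase alone suggests. Clinical relevance comes first, and on a natural reading the two criteria are alternative grounds for inclusion. Age, FSH and AFC would then probably enter whatever their balance. This stands to the extent that the text does not exclude age. It does not require age either, and the imbalance ground remains a poor rule beside it.

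Three stronger readings are tempting and are not supported.

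- **That efficacy will be reviewed by arm before the SAP is settled.** The Data management section lists efficacy endpoints as a topic and mentions no results by arm. The Data Management Report is prepared before database lock, and the locked database goes to the statisticians. The Blinding section blinds the analysts. Investigators are not listed as blinded, but that does not make them unblinded. What stands is that the meeting is not stated to be blinded.
- **That the p < 0.10 rule inflates false positives.** Applied mechanically it does not. The 8–11% arises only if someone picks the most favourable subset after seeing results, which the text does not describe. It measures what an open list would permit.
- **That the model will be overfitted by 13 centre effects plus every listed term.** The section says only that centres may be included. It gives no coding and does not say that all candidates enter together. The documents do not give centre sizes, so no rate of failed fits can be derived from them.

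**Conclusion.** The concern holds as a badly chosen selection rule that the protocol states, not as detail left to an SAP. An SAP could not cure it by adding detail; it would have to replace the rule.

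The harm is that the primary model and its conditional odds ratio depend partly on chance imbalance and partly on an open choice, and that adjustment for the stratification factor is not assured. The size is a 34% to 41% chance of at least one imbalance flag, assuming independent baseline items. Type I error is about 4% if the rule is followed mechanically. With unrestricted choice among 16 subsets it is about 8–11%, under the assumed covariate effects. The documents do not show that such a choice will be made or that efficacy will be seen by arm. The point should be corrected, but it does not by itself invalidate the primary test.

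**What to change.** 1. In the Statistical analysis section, delete the p < 0.10 criterion and the open list. Pre-specify the primary model as arm, age stratum (<35/≥35), baseline FSH and baseline AFC, with centre as a random intercept or pooled by region.
2. State that the primary model uses baseline variables only, so that retrieved oocytes, type of transfer and number of embryos transferred are not in it.
3. In the Data management section, either finalise the SAP before any efficacy data are listed, or state that the Data Review Meeting is blinded to arm and cannot change the primary model.

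The cost is SAP wording and an earlier sign-off. No new data are needed: demographic data, FSH and AFC are already scheduled at screening in Table 1.

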#### Secondary outcomes

The secondary outcomes include the number of follicles ≥ 14 mm, E2 level, and endometrial thickness on the hCG trigger day; the number of retrieved oocytes, metaphase II (MII) oocytes, and two pronuclei (2PN) fertilizations; as well as the rates of 2PN fertilization, available embryos, high-quality embryos, implantation, cycle cancellation, biochemical pregnancy, pregnancy loss, sustained pregnancy, and live birth. The outcomes of IVF-ET and their definitions are summarized in **Table 4**. While the post-treatment observation will be terminated at about 24 weeks, data on live birth will be obtained through the participating centers’ mandatory, complete follow-up system extending to the end of pregnancy.

**Table 4 T4:** Diagnosis definitions of IVF-ET outcomes.

Diagnosis	Definition
Primary outcomes	
clinical pregnancy rate (CPR)	the number of clinical pregnancies divided by the total number of embryo transfer cycles.
Secondary outcomes	
Outcomes of IVF-ET	
2PN fertilization rate	the number of 2PN embryos divided by the number of MII oocytes
available embryo rate	the number of transferable embryos divided by the number of 2PN fertilization
high-quality embryo rate	the number of high-quality embryos divided by the number of normally fertilized cleavage embryos. High-quality embryos were defined based on the day of embryo transfer, according to the Istanbul consensus and Gardner criteria, as follows: Day 2: embryos with 4 cells, <10% fragmentation, and absence of multi-nucleation; Day 3: embryos with 8 cells, <10% fragmentation, and no multi-nucleation; Day 5: blastocysts at stage 4, with inner cell mass and trophectoderm both graded as A (17, 18).
Implantation rate	the number of gestational sacs divided by the number of embryos transferred.
cycle cancellation rate	the number of cancelled embryo transfer cycles divided by the number of embryo transfer cycles
biochemical pregnancy rate	the number of patients with positive serum b-hCG pregnancy test results divided by total embryo transfer cycles
pregnancy loss rate	the number of pregnancy termination cycles within 12 weeks divided by the number of embryo transfer cycles
sustained pregnancy rate	the number of cycles of pregnancy greater than 12 weeks divided by the number of embryo transfer cycles
live birth rate	the number of live births divided by total embryo transfer cycles.
Scale measurement	

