Furthermore, the predominant number of individuals diagnosed with DOR manifest symptoms of anxiety to varying extents. The utilization of the SAS, a tool specifically developed to gauge anxiety and psychological stress, will serve to evaluate the levels of anxiety present in DOR women (30).

Acupuncture has been shown to modulate gonadotropin levels, lowering FSH, LH, and the FSH/LH ratio, while elevating E2 and ameliorating emotional symptoms in DOR patients, with a favorable safety profile (9–11). Research indicated that acupuncture contributes to higher CPR in IVF-ET for DOR women by effectively improving their underlying ovarian reserve function (31). Another investigation demonstrated that acupuncture positively influences hCG-day estrogen levels, endometrial conditions, thereby improved endometrial receptivity during IVF-ET (32). However, existing trials are limited by small sample sizes. This large-sample, multicenter RCT is designed to definitively assess the efficacy and safety of the acupuncture intervention, thereby addressing this critical evidence gap.

According to traditional Chinese medicine (TCM) theory, an imbalance of the Ren Meridian (Conception Vessel, CV) and Chong Meridian (Penetrating Vessel, PC) constitutes a fundamental pathogenesis of DOR, and is associated with kidney deficiency, liver stagnation, and spleen deficiency. Therefore, the main therapeutic principles for DOR involve regulating the Chong and Ren Meridians, tonifying the kidney, regulating the liver and fortifying the spleen. During this clinical trial, the selected acupuncture points will include CV 12 (Zhongwan) and CV 4 (Guanyuan) from the Ren Meridian; KI 12 (Dahe) and KI 16 (Huangshu), which are intersection points of the Kidney Channel of Foot-Shaoyin and the Chong Meridian; SP 6 (Sanyinjiao), which serves to invigorate the kidney, regulate the liver, and fortify the spleen; BL 23 (Shenshu), BL 33 (Zhongliao), and KI 3 (Taixi), which are utilized to reinforce the kidney and nourish the essence; and LR 3 (Taichong), which alleviates liver tension and harmonizes qi.

The methodological rigor of this trial, particularly regarding randomization, allocation concealment, and blinding across all study stages, will be safeguarded by the use of placebo needles, adhesive pads, and an EDC system.

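### The primary model for clinical pregnancy may adjust for retrieved oocytes, type of transfer and number of embryos transferred, all of which are settled only after randomised treatment

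*Protocol article*

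**What the plan says.** The protocol article, under Statistical analysis, applies the intention-to-treat principle throughout and estimates an adjusted odds ratio for clinical pregnancy by logistic regression. Covariates are chosen "based on their established clinical relevance to IVF outcomes and any observed baseline imbalances between groups (p < 0.10". The candidates follow: "These covariates may include centers, age, baseline FSH level, AFC, COH protocol, number of retrieved oocytes, type of ET, number of embryos transferred, etc".

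Other sections bear on three of these candidates:

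- **Timing.** Under Acupuncture group, treatment starts two menstrual cycles before the IVF cycle, lasts about ten weeks and runs up to retrieval. The oocyte count is therefore known when treatment ends, and the transfer comes later.
- **Oocytes as an outcome.** Secondary outcomes lists "the number of retrieved oocytes, metaphase II (MII) oocytes, and two pronuclei (2PN) fertilizations".
- **Mechanism.** The Discussion cites research that "acupuncture contributes to higher CPR in IVF-ET for DOR women by effectively improving their underlying ovarian reserve function".
- **Transfer.** Primary outcome counts the first transfer whether fresh or frozen. The inclusion criteria give only a plan for the number and stage of embryos.

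Nothing in the article limits the primary model to baseline variables, and no unadjusted or baseline-only primary analysis is named.

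**The concern.** In a randomised trial, covariates in the primary model should be variables that treatment cannot have changed. A variable measured after treatment can carry part of the effect. Holding it constant then compares women with equal oocyte yield, although a different yield is one of the things acupuncture is meant to produce. The resulting odds ratio no longer estimates the effect of being assigned to acupuncture, which is what an intention-to-treat analysis is for.

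There is a second mechanism. If some unmeasured prognostic factor drives both oocyte yield and pregnancy, conditioning on yield makes the arms differ in that factor, and the direction of the resulting bias is not known beforehand.

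The section also conflicts with itself. Its selection rule speaks of baseline imbalance, but these three candidates are not baseline variables. At stake are the headline odds ratio and the power to detect it.

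**Working it through.** **Inputs from the article.** Sample size assumes "the CPR of IVF-ET in DOR patients after acupuncture pretreatment would be 38%, compared to 22% following placebo acupuncture pretreatment". It continues: "A sample size of 120 participants per group has been determined to ensure 80% statistical power, with a two-sided alpha of 0.05". Then: "An initial total of 300 participants (150 per group) will be enrolled to allow for an anticipated 20% dropout rate". Allocation is "in a 1:1 allocation ratio, employing stratified block randomization by age".

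**The plan's own figure.** With p1 = 0.38, p2 = 0.22 and mean 0.30, the pooled formula is

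n = [1.960·√(2·0.30·0.70) + 0.842·√(0.38·0.62 + 0.22·0.78)]² / 0.16² = (1.270 + 0.537)² / 0.0256 ≈ 127.6, so 128 per group.

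Other common two-sided forms give 125 (unpooled), 127 (arcsine), 132 (log-odds ratio) and 140 (continuity-corrected). The stated 120 is not reproduced. Power at 120 is Φ[(0.16·√120 − 1.270)/0.638] = Φ(0.756) = 77.5%. The dropout step does reproduce: 120/0.8 = 150. The small shortfall is a separate matter; it only means that the reference power below is about 77–80%. The marginal odds ratio is (0.38/0.62)/(0.22/0.78) = 2.17.

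**Model for the adjustment (assumed).** The article gives no effect on oocytes and no strength of association with pregnancy, so both are varied. T is the arm (0 or 1) and M a standardised mediator:

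- M = a·T + N(0,1)
- logit P(pregnancy) = b0 + c·T + b·M

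Here a is the shift in SD caused by acupuncture and b the log-odds ratio per SD. For each pair, b0 and c are solved so that the marginal rates stay at 22% and 38%. A model with T alone targets the marginal odds ratio of 2.17; a model with T and M targets exp(c). Each row below rests on 3,000 simulated trials of 120 per arm.

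| b | a | exp(c) | Median OR, M left out | Median OR, M adjusted | Power, M left out | Power, M adjusted |
|---|---|---|---|---|---|---|
| 0.3 | 0 | 2.20 | 2.22 | 2.24 | 78.4% | 78.8% |
| 0.3 | 0.2 | 2.08 | 2.17 | 2.09 | 77.3% | 70.9% |
| 0.3 | 0.4 | 1.95 | 2.19 | 1.98 | 76.7% | 63.1% |
| 0.3 | 0.6 | 1.84 | 2.17 | 1.84 | 77.4% | 51.5% |
| 0.5 | 0 | 2.26 | 2.19 | 2.29 | 78.4% | 79.5% |
| 0.5 | 0.2 | 2.04 | 2.18 | 2.06 | 77.7% | 67.8% |
| 0.5 | 0.4 | 1.85 | 2.18 | 1.85 | 78.1% | 53.9% |
| 0.5 | 0.6 | 1.67 | 2.19 | 1.68 | 78.0% | 40.1% |
| 0.8 | 0 | 2.39 | 2.19 | 2.42 | 77.8% | 81.6% |
| 0.8 | 0.2 | 2.04 | 2.19 | 2.04 | 78.5% | 65.1% |
| 0.8 | 0.4 | 1.74 | 2.17 | 1.74 | 77.7% | 43.2% |
| 0.8 | 0.6 | 1.48 | 2.22 | 1.50 | 79.6% | 23.9% |

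**Check by hand.** For a given b, fixing the 38% rate fixes c + a·b. Hence exp(c) at shift a equals its value at zero shift times exp(−a·b). In the middle case this is 2.26·exp(−0.4·0.5) = 2.26·0.819 = 1.85. In the most extreme case it is 2.39·exp(−0.6·0.8) = 2.39·0.619 = 1.48. Both agree with the table.

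With a = 0 the adjusted odds ratio rises slightly, because a conditional odds ratio lies further from 1 than a marginal one. Nothing is lost in that case. The model contains no unmeasured common cause of M and pregnancy, so the range shows only the loss of the mediated part and not the second source of bias.

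**The case against.** The strongest defence is that the wording is permissive, that the statistical analysis plan is not shown and could exclude these variables, and that all three are recognised predictors of IVF success. The first two parts stand as qualifications: the harm arises only if the variables are selected and acupuncture shifts them. They do not remove the point, because the article names the variables as candidates for its primary model. Prognostic value does not justify adjusting a randomised comparison for something that treatment may change.

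A reader might also infer more than the article supports:

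- **That all three are mediators.** Only oocyte yield is tied to the stated mechanism. The article does not say that acupuncture changes the type of transfer or the number of embryos transferred. They are post-randomisation variables that it could affect.
- **That the whole effect would vanish or reverse.** The Discussion also cites a route through endometrial receptivity, which adjusting for oocytes need not remove. In the model above, complete mediation needs c = 0, that is a shift of ln(2.39)/0.8 = 1.09 SD to ln(2.20)/0.3 = 2.63 SD, and even then the adjusted odds ratio is 1.0. Going past 1 needs a further ingredient, such as an unmeasured common cause, on which the article gives no figures.
- **That the covariates drop women who have no transfer.** Clinical pregnancy rate is defined per transfer cycle, so on that definition these women are outside the primary outcome whatever the covariates.
- **That 38% and 22% are known to be total effects.** The article does not say whether the source rates are crude or adjusted, or per woman or per transfer. The calculation uses them as marginal rates by assumption.

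**Conclusion.** The point holds. The primary model as described admits three variables determined after randomised treatment. For retrieved oocytes the conflict is internal: the trial tests it as an outcome, cites ovarian reserve as the route to pregnancy, and then offers yield as an adjustment variable. For type of transfer and number transferred, their timing is reason enough to leave them out.

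The size is conditional. If acupuncture shifts the mediator by 0.2 to 0.6 SD and each SD carries a log-odds ratio of 0.3 to 0.8, the odds ratio falls from about 2.2 to between 2.09 and 1.50, and power at 120 per arm from about 77–80% to between 71% and 24%. In the middle case it falls from 2.18 to 1.85, and power from 78% to 54%. With zero shift there is no loss. Attenuation is what the stated mechanism would lead one to expect, but bias in the other direction cannot be excluded. Because the headline estimate is affected and the remedy is cheap, this should be corrected before outcome data are reviewed.

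**What to change.** Delete number of retrieved oocytes, type of transfer and number of embryos transferred from the primary model, together with the open ending of the list. Prespecify only variables fixed before randomisation: age stratum, centre, baseline FSH, baseline AFC, and COH protocol as planned at enrolment.

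Two of these need exact wording. AFC is measured both at screening and in the IVF cycle, so the text should say baseline AFC. COH starts only after at least eight weeks of treatment, so the covariate should be the protocol planned at entry and not the one used.

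A fixed list also leaves no role for choosing covariates by p < 0.10. Any model containing post-randomisation variables can be reported as a labelled exploratory mediation analysis.

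The cost is about one sentence in the protocol and the same in the analysis plan. No further participants are needed, and no new data beyond having the planned COH protocol on record before randomisation.
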